The second transfusion topic will be used to determine whether the results can be replicated and generalised. We have decided to randomise the four feedback interventions to clusters separately for each topic using a “split-block” type of design,  rather than keep the allocations the same across topics within trusts, to ensure that our estimates of their effects are unbiased across trials, relying on the design to separate the effects of the feedback interventions from time and topic, increasing the robustness of the conclusions drawn about the second trial. Outcome results for the first trial will not be made available outside of the statistical team until results of the second trial are also available.

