## 9 Randomisation of NHS Trusts / Health Boards

The NCA will inform the CTRU, University of Leeds, when each baseline audit is complete and the audit database has been locked for analysis.

Trusts or Health Boards will be randomised by the CTRU using an automated randomisation system based at the CTRU. It will remain possible to participate in each topic until each baseline audit database has been locked.

Trusts or Health Boards that fulfil the eligibility criteria, have NHS Permissions to participate and have completed the baseline audit will be randomised on a 1:1:1:1 basis to receive one of four feedback interventions twice, once after each baseline audit.

A computer-generated minimisation programme incorporating a random element will be used to ensure intervention arms are balanced for the following cluster-level characteristics:

- Trust size. For each audit we will review the number of cases submitted to baseline audit per cluster and then break these down into tertiles (Large, Medium and Small); the final cutpoints used will then be reported. This data was provided by the NCA after the close of audit data collection.
- Regional Transfusion Committee (RTC): refer to Appendix C for details of the RTC

For the second randomisation to the haematology audit, an additional stratification factor will be used which will include the previous randomised allocation to the first trial.

Where Trusts or Health Boards merge following each randomisation they will continue to be regarded as separate and distinct clusters for intervention, data collection and analysis purposes. For clusters that merge between trials dependent upon review these will continue to be regarded as distinct clusters as well. This will be accounted for in a sensitivity analysis.

Following each randomisation, the CTRU will inform the NCA, the Chief Investigators and the intervention delivery team so that appropriate arrangements can be made to facilitate the development and the delivery of the feedback according to randomised allocation.

Other personnel involved in the trial will only be informed of intervention allocation if this is required to undertake their role associated with the trial. A log will be maintained of who is unblinded to what at specific points in the research process.

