## 16.2 Sample size

The sample size calculation has been refined following the grant application in light of decisions regarding the feedback interventions and transfusion topics. For each topic, there are two principal comparisons of interest (1. enhanced feedback documents vs. usual documents; and 2. Post-feedback support vs. no post-feedback support), relating to the two main effects of the 2X2 factorial design. Assuming that there will be 20% unnecessary transfusions at follow-up for each topic, that the ICC will be 0.05 and that cluster sizes will vary from 17 to 68 with a mean of 45, we need 152 clusters to detect a minimally important reduction of 6% (i.e. to 14% unnecessary transfusions) in the presence of, at most, a small antagonistic statistical interaction (i.e. 10% or fewer unnecessary transfusions in the enhanced feedback documents and post-feedback support) with 80% power using logistic regression models, with a random-intercept for cluster, and a 2-sided 2.5% significance level, for each comparison within each model. This requires us to recruit from England, Wales, Scotland and Northern Ireland and allows 12/171 (7%) clusters to be ineligible and 95% of those eligible to consent and be randomised. If these assumptions do not all hold, the tables below illustrate the impact on the minimally important clinical difference the trial would be powered to detect.

**Table 2: Sensitivity Analyses for ICC and recruitment assumptions fixing the power to detect the main effects at 80% & baseline proportion of unnecessary transfusions at 20%**

| ICC         | 150 Clusters   | 140 Clusters    | 130 Clusters    |
|-------------|----------------|-----------------|-----------------|
| 0.05 | (20, 14, 10.0) | (20, 13.5, 9.8) | (20, 13.0, 9.5) |
| 0.06 | (20, 13, 9.5)  | (20, 12.5, 9.3) | (20, 12.5, 8.9) |

|             |               |                 |                 |
|-------------|---------------|-----------------|-----------------|
| 0.07 | (20, 13, 9.0) | (20, 12.0, 8.8) | (20, 12.0, 8.4) |
| 0.08 | (20, 12, 8.5) | (20, 11.5, 8.3) | (20, 11.5, 7.9) |
| 0.09 | (20, 12, 8.0) | (20, 11.0, 7.8) | (20, 11.0, 7.4) |
| 0.10 | (20, 11, 7.8) | (20, 10.5, 7.5) | (20, 10.5, 7.0) |

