### **16.3.4 Primary endpoint analysis**

For each topic independently, the patient-level binary primary outcome of unnecessary transfusions 12 months following randomisation will be analysed using logistic regression, with a random intercept for trust/health board, adjusting for design factors (that is, trust size, regional transfusion committee, and trust-level proportion of unnecessary transfusions at baseline), with contrasts for (1) enhanced vs. standard documents, (2) post-feedback support vs. no post-feedback support, and (3) the interaction between (1) and (2).

Unadjusted and adjusted intra-cluster correlations (ICCs) and corresponding 95% confidence intervals will be presented. We will report the estimates and two-sided 97.5% confidence intervals for the two main effects from this model.

In addition to sensitivity analyses relating to assumptions about the missing data mechanism we will also analyse the supportive outcomes that include a grey-area category using ordinal logistic regressions and look for consistency in the size, direction and interpretation of effect.

Following the analysis of each topic independently, a further analysis will be conducted using data from both audit topics. This analysis uses a bivariate patient-level binary primary endpoint outcome of unnecessary transfusions 12 months following randomisation and will be analysed using multivariate logistic regression, with a random intercept for trust/health board and will be adjusted for the same design factors as above and additionally controlled for audit topic. The model will then include contrasts for (1) enhanced vs. standard documents, (2) post-feedback support vs. no post-feedback support and (3) the interaction between (1) and (2). We will then fit all possible interactions between (1), (2), (3) and audit topic; we do this in order to get unbiased estimators for the general effects of interventions accounting for possible interactive effects between the two trials on the intervention effects. Unadjusted and adjusted intra-cluster correlations (ICCs) and corresponding 95% confidence intervals will be presented. We will report the estimates and two-sided 97.5% confidence intervals for the two main effects from this model and also for the interactions between (1) and (2) and audit topic.

The same sensitivity analyses will be run on this model as with the separate models.

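### The combined two-topic model names one random intercept per trust although each trust is re-randomised for each topic; read literally, its 97.5% intervals are too narrow unless trust effects are perfectly correlated across topics

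*Protocol*

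**What the plan says.** Protocol section 7 explains that the plan is to "randomise the four feedback interventions to clusters separately for each topic using a “split-block” type of design". The same sentence sets out the option it turned down and its reason: "rather than keep the allocations the same across topics within trusts, to ensure that our estimates of their effects are unbiased across trials". Section 9 confirms that trusts are "randomised on a 1:1:1:1 basis to receive one of four feedback interventions twice, once after each baseline audit". For the haematology trial it adds that "an additional stratification factor will be used which will include the previous randomised allocation to the first trial".

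Section 16.3.4 first analyses each topic on its own, by logistic regression with a random intercept for trust. It then adds a pooled analysis, whose outcome is described thus: "This analysis uses a bivariate patient-level binary primary endpoint outcome of unnecessary transfusions 12 months following randomisation". As to the model, the protocol says that this outcome "will be analysed using multivariate logistic regression, with a random intercept for trust/health board and will be adjusted for the same design factors". Audit topic is an additional covariate, and a later sentence reads: "We will then fit all possible interactions between (1), (2), (3) and audit topic". Intervals at 97.5% are to be reported for the two main effects and for their interactions with topic.

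No topic-specific or trust-by-topic random term is named anywhere. Section 16.3.1 describes the general approach as a random intercept model with one cluster-level and one patient-level variance, held equal across arms.

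**The concern.** In a per-topic model the trust is the randomised unit, and one intercept per trust is right. In the pooled data the randomised unit is the trust within a topic. Many trusts will have one level of a factor for surgery and the other for haematology, and for those trusts the pooled model estimates the effect from the difference between the trust's own two topics. With a single shared intercept, the only error set against that difference is patient-level binomial noise. Any real tendency of a trust to do better in one topic than in the other is treated as if it did not exist.

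Perfect agreement is hard to assume here. The topics use different algorithms for an unnecessary transfusion, haematology adds platelets, the specialties differ, and the audits run one after the other.

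At stake are the two results for which the pooled model exists: the general effect of each intervention, and whether the effects differ by topic (the last secondary objective in section 6.2). Intervals that are too narrow could suggest a general effect, or a difference between topics, that is not there.

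**Working it through.** **1. The plan's own figure.** Section 16.2 assumes "that the ICC will be 0.05 and that cluster sizes will vary from 17 to 68 with a mean of 45", with 20%, 14%, 14% and 10% in the four arms and a two-sided 2.5% level. The protocol gives no coefficient of variation (CV) of cluster size, so CV 0.29 is assumed.
- Design effect: 1 + ((1 + 0.29²) × 45 − 1) × 0.05 = 3.389.
- Effective size per arm: 38 × 45 / 3.389 = 504.6.
- Main effect: mean of the two simple log odds ratios, (0.429 + 0.382)/2 = 0.405.
- SE: ½ × √[(1/0.16 + 2/0.1204 + 1/0.09)/504.6] = 0.130.
- Power: Φ(0.405/0.130 − 2.241) = 81.2%, with 147.9 clusters needed for 80%. At CV 0.33, power is 80.5% and 150.4 clusters are needed.

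The stated 152 clusters are reproduced. They refer to a single topic; the protocol gives no power or precision for the pooled model.

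**2. Inputs for the pooled model.** 152 trusts in both topics, mean size 45, 20% rate, no intervention effect, second allocation balanced within the first. Write σ² for the trust variance on the log-odds scale and ρ for the correlation of a trust's effects across topics. ρ is an assumption, varied from 0 to 1. ICC 0.05 on the latent scale gives σ² = (0.05/0.95) × π²/3 = 0.173. A larger value, 0.39, represents an ICC on the proportion scale. By numerical integration at a 20% rate, 0.39 corresponds to an ICC of 0.058, and exactly 0.05 needs σ² = 0.33.

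**3. Closed-form approximation for one main effect.** Sampling variance of a trust's log odds in one topic: e = 1/(45 × 0.2 × 0.8) = 0.139. With balanced allocations, 76 trusts have the same level of a factor in both topics and 76 have different levels.
- Same level, between trusts: variance 4[σ²ρ + (σ²(1−ρ) + e)/2]/76. The shared-intercept fit gets this part about right.
- Different levels, within trust: true variance 2[σ²(1−ρ) + e]/76, but the model uses 2e/76.

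For σ² = 0.173 and ρ = 0.5:
- Between: 4[0.0865 + (0.0865 + 0.139)/2]/76 = 0.01048, information 95.4.
- Within, as the model sees it: 2 × 0.139/76 = 0.00365, information 273.6.
- Model SE: 1/√(95.4 + 273.6) = 0.052. Weights: 0.259 between, 0.741 within.
- Within, true: 2 × (0.0865 + 0.139)/76 = 0.00593.
- True SE: √(0.259² × 0.01048 + 0.741² × 0.00593) = 0.063.
- Ratio 1.21; coverage 2Φ(2.241/1.21) − 1 = 93.6%.

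**4. Simulation.** 900 runs per setting, maximum likelihood with quadrature, one trust intercept, all topic interactions fitted, nominal 97.5% Wald intervals. In the setting just worked, the mean model SE was 0.053 and the empirical SD 0.065.

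| σ² | ρ | True SE / model SE (closed form) | Coverage, closed form | Coverage, simulated |
|---|---|---|---|---|
| 0.173 | 0 | 1.36 | 90.0% | about 89% |
| 0.173 | 0.5 | 1.21 | 93.6% | about 93% |
| 0.173 | 0.9 | 1.05 | 96.8% | about 96.5% |
| 0.173 | 1 | 1.00 | 97.5% | about 97% |
| 0.39 | 0 | 1.80 | 78.8% | about 77% |
| 0.39 | 0.5 | 1.48 | 87.1% | about 86% |
| 0.39 | 0.9 | 1.12 | 95.6% | about 95% |
| 0.39 | 1 | 1.00 | 97.5% | about 97.5% |

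At σ² = 0.33 the closed form gives 81.7%, 88.9% and 95.9% for ρ = 0, 0.5 and 0.9, so the 0.39 rows are slightly pessimistic for an ICC of exactly 0.05. Topic interactions behaved like the main effects. Since all topic interactions were in the fitted model, including them does not cure the problem.

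**5. With a trust-by-topic intercept added** (σ² = 0.173, ρ = 0.5, 250 runs): mean SE of a main effect 0.061 against an SD of 0.064 to 0.066; coverage 95.2 to 97.2% for main effects and 97.2 to 97.6% for topic interactions. Monte Carlo error is about 1 point, so coverage is largely restored.

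**The case against.** The strongest reply is that the sentence may already describe the right model. *Bivariate* and *multivariate* are used only for the pooled analysis, and in a multivariate multilevel model a random intercept ordinarily means one per response, with a covariance. Control for audit topic does not rule this out, because such models are often fitted to stacked data with a topic indicator. On that reading the standard errors are adequate. This part stands: the intention may be right. But the random-effect phrase is the one used for the per-topic models, where it can only mean one value per trust. The bivariate label is also attached to the patient, whereas section 13.7 says patients cannot be linked. Dependence between topics can be modelled only at trust level, which is where the text names a single intercept.

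A second reply is that covariance structure is normally left to the SAP. That would hold had the protocol been silent, but it fixes both the random effect and the intervals to be reported.

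A third reply is that the size is assumed, and that adjustment for baseline proportion, trust size and region would absorb some of the variation. This stands in part. In a further simulation with 144 trusts, type I error against a nominal 2.5% ran from 5.4% to 16.4% for correlations of 0.8 down to 0 at ICC 0.05, and from 4.2% to 10.1% if covariates cut the residual ICC to 0.03. The loss is smaller but not removed.

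A reader might also infer that the reported main effects average over topics only under one particular coding of topic. The protocol does not support that: an average over topics can be obtained as a contrast under any coding, and the plan speaks of contrasts.

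**Conclusion.** The point holds conditionally. If the pooled model has one scalar intercept per trust, as the words literally say, it omits variation at the level where treatment is allocated, and its 97.5% intervals under-cover whenever the cross-topic correlation is below 1. At ICC 0.05, coverage is about 95 to 96.5% at correlation 0.9, about 86 to 93% at 0.5, and about 77 to 89% at 0. The lower figures come from a trust variance slightly above what ICC 0.05 implies on the proportion scale. The figures rest on an assumed correlation, no covariate adjustment, and all 152 trusts taking part in both topics.

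Two stronger readings are tempting. One is that the intervals are wrong whatever the truth; they are not, since the loss vanishes at correlation 1 and is small near it. The other is that the trial's primary results are compromised. Sections 6.1 and 16.3.2 treat the topics as two trials, each with its own primary analysis in which one intercept per trust is correct, and the sample size was set for those models. Only the further, pooled analysis is affected.

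**What to change.** State in section 16.3.4, and carry into the SAP, that the combined model has topic-specific random intercepts for each trust or health board with an unstructured 2x2 covariance (equivalently, a trust intercept plus a trust-by-topic intercept). Add that *bivariate* refers to the trust level, because patients are not linked across topics. The same sentence serves whether the present text is an error or only unclear.

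The cost is one or two extra variance parameters and wider intervals. In the setting with σ² = 0.173 and correlation 0.5, the main-effect SE rises from 0.053 to 0.061, about 15%. If the correlation is in fact near 1, little precision is lost. No change is needed to the per-topic analyses, the sample size or data collection.

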### **16.3.5 Secondary endpoint analyses**

The patient-level secondary endpoints for both trials covering volume transfused (both RBC and platelets) will be analysed using a Poisson random intercept regression model, with the same contrasts and adjusting for the same covariates as in the primary endpoint analysis. The trust-level secondary endpoints (volume transfused, number of SHOT-reportable incidents, and number of definitely, probably or possibly preventable incidents reported to SHOT within clinical specialities targeted by the audit) will be analysed using cluster-level analyses recognising the outcomes are all counts, again with the same contrasts and adjusting for the same covariates as in the primary endpoint analysis.

We will additionally analyse the supportive outcomes relating to the volume of transfused. The first two will act as sensitivity analyses for the trust-level analysis, indicating whether the size, direction and interpretation of the effect depend on the type of BSMS data summarised. The second three will act as a sensitivity analysis for the patient-level analysis, indicating whether the size, direction and interpretation of the effect depend on the stage in the operative process.

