### **5.2.5 Baseline versus Follow-Up Audits**

For each topic, there will be a baseline audit and a follow-up audit approximately 12 months following randomisation. The follow-up audit will include the subset of the items included in the baseline audit required to calculate outcomes.

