### **13.3 Clinical Audit Data**

To minimise the risk of detection bias, the NCA team will develop a *Data Collection Protocol* outlining how data are to be collected and will provide the data collectors with training in the clinical audit prior to the start of the audit. It is acknowledged that prior experience in clinical audit and the review of medical records may improve the quality of reporting. Availability of data collectors at the host organisation may also determine who can perform the audit. Therefore the NHS Trust / Health Board will be responsible for identifying the data collectors, with preference given for the people independent from the hospital transfusion team and the transfusion committees.

The NCA will ask NHS Trusts / Health Boards participating in the audit to collect data using supplied proformas and then key it into an online form or it will be keyed directly online depending on preference. Alternatively, NHS Trusts / Health Boards may transfer the completed proformas to the NCA who will then key it into the online form. Audit data will be retained in line with best practice.

The NCA will provide CTRU with four fully-anonymised patient level datasets, covering the baseline and follow-up audits for each of the two transfusion topics. The data will be provided in electronic format, via a secure file transfer system. The first dataset relating to the first audit topic will include the following variables:

All eligible cases during the reporting period:

- Consecutive unique patient ID
- Year of birth
- Sex
- Type of procedure
- Date of decision for surgery
- Patient status at time of audit (i.e. audited or notes not available)

All cases that can be audited:

- Investigations for anaemia
- Date of planned surgery
- Pre-operative treatment of anaemia
- Details of pre-operative transfusion (incl. pre-op Hb, volume of RBC, reason)
- Pre-operative acute coronary ischaemia
- Pre-operative medications (type, whether stopped)
- Date of actual surgery
- Details of intra-operative transfusion (incl. intra-op Hb, cell-salvage/allogeneic RBC, reason)
- Intra-operative medications (adjuvant treatments)
- Post-operative cell salvage (technique, volume)
- Post-operative complications
- Details of post-operative transfusions (incl. post-op Hb, volume RBC, reason)
- Date of discharge or death

This dataset will then be sent again for the follow-up audit.

For the second trial the dataset will include the following variables:

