### **16.1.2 Secondary endpoints**

For the surgical audit *secondary outcomes* are:

1. Total volume of allogeneic RBC transfused (Units at trust-level, from BSMS summed over blood groups and clinical specialities, calculated from net-issue minus wastage)
2. Total volume of allogeneic RBC transfused (Units at patient-level, from NCA summed over pre-operative, intra-operative and post-operative periods);
3. Total number of incidents reported to SHOT (Count at trust-level, from SHOT summed over clinical specialities and events, near misses and “right blood right patient” incidents)
4. Number of definitely, probably or possibly preventable incidents reported to SHOT within clinical specialities targeted by the audit (Count at trust-level, from SHOT summed over events, near misses and “right blood right patient” incidents)

For the Haematology audit *secondary outcomes* are:

1. Total volume of allogeneic RBC transfused (Units at trust-level, from BSMS summed over blood groups and clinical specialities, calculated from net-issue minus wastage)
2. Total volume of allogeneic RBC transfused (Units at patient-level, from NCA)
3. Total volume of platelets transfused (Units at trust-level, from BSMS summed over clinical specialities, calculated from net-issue minus wastage)
4. Total volume of platelets transfused (Units at patient-level, from NCA)
5. Total number of incidents reported to SHOT (Count at trust-level, from SHOT summed over clinical specialities, and events, near misses and “right blood right patients incidents)
6. Number of definitely, probably or possibly preventable incidents reported to SHOT within clinical specialities targeted by the audit (Count at trust-level, from SHOT summed over events, near misses and “right blood right patient” incidents)

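### The patient-level transfused-volume models adjust for the trust's baseline proportion of unnecessary transfusions but not for its baseline mean units per patient, which gives away precision

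*Protocol*

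**What the plan says.** Section 16.1.2 defines three patient-level volume outcomes taken from the national audit (NCA). Surgical secondary outcome 2 is allogeneic red cell volume ("Units at patient-level, from NCA summed over pre-operative, intra-operative and post-operative periods"). Haematology secondary outcomes 2 and 4 are red cell and platelet units per patient.

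Section 16.3.5 says of these endpoints: "will be analysed using a Poisson random intercept regression model, with the same contrasts and adjusting for the same covariates as in the primary endpoint". Section 16.3.4 gives the list that is carried over: "trust size, regional transfusion committee, and trust-level proportion of unnecessary transfusions at baseline". No baseline value of volume appears in it.

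On what is known at baseline, section 5.2.5 states: "The follow-up audit will include the subset of the items included in the baseline audit required to calculate outcomes". Section 13.3 says that the baseline and follow-up patient-level datasets for both topics go to the CTRU. Section 9 randomises only trusts that have completed the baseline audit.

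**The concern.** The primary model adjusts for the trust-level baseline of its own outcome. That variable is called a design factor, but section 9 minimises only on trust size and RTC (plus the earlier allocation in the second trial). Its role in the primary model therefore appears to be that of a baseline measure of the same outcome. Copied into a model for units per patient, it loses that role, because a trust can give few unnecessary transfusions and many units per patient, or the reverse.

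Different patients are audited at baseline and follow-up (section 7), so a trust-level summary is the natural baseline adjustment. Without it, stable between-trust differences in volume stay in the error term and the intervals on the volume effects are wider than they need be. Chance differences between arms in baseline volume also go unadjusted: size is minimised as tertiles of audit case numbers, which does not balance units per patient. Volume in the targeted specialities is a stated secondary objective (section 6.2).

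**Working it through.** **The plan's own figure.** Section 16.2 gives power for the primary outcome only. From cells of 20, 14, 14 and 10%, 38 clusters of mean size 45 per cell, ICC 0.05 and 2-sided 2.5%, the main effect on the logit scale is (logit 0.10 − logit 0.20)/2 = −0.405. The coefficient of variation of cluster size is not stated. Assuming 0.25 to 0.33 from the range 17 to 68, power is 81.8% to 80.5%, which agrees with the stated 80% at 152 clusters. No power or precision figure is given for volume, so the rest depends on assumptions.

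**Inputs**
- m = 45 patients per cluster and alpha = 0.025 two-sided: section 16.2.
- ICC for volume: not in the protocol. The value 0.05 is borrowed from the binary primary outcome; 0.02 is a lower alternative.
- c, the correlation between a trust's underlying effect at baseline and at follow-up: assumed 0.5 to 0.8.
- ρ, the trust-level correlation between volume and the unnecessary proportion: assumed 0 to 0.6.
- Planned power 80% for some volume effect: a reference point, since the protocol sets none.

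**Formulas** (cluster-mean approximation, equal cluster sizes, the same reliability for both baseline measures)
1. Reliability of a trust mean: R = m·ICC/(1 + (m − 1)·ICC). At ICC 0.05, 2.25/3.20 = 0.703. At ICC 0.02, 0.90/1.88 = 0.479.
2. Correlation of the follow-up mean with own baseline: a = c·R. With the baseline unnecessary proportion: b = c·ρ·R. Between the two baseline measures: d = ρ·R.
3. Residual variance with both covariates, relative to the planned covariate alone: V = [1 − (a² + b² − 2abd)/(1 − d²)]/(1 − b²).
4. Power after the change: Φ((2.241 + 0.842)/√V − 2.241).

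**Example**, ICC 0.05, c = 0.5, ρ = 0: a = 0.352 and b = 0, so V = 1 − 0.124 = 0.876. Power = Φ(3.083/0.936 − 2.241) = 85%.

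| ICC | c | ρ | V | Power |
|---|---|---|---|---|
| 0.05 | 0.5 | 0 | 0.876 | 85% |
| 0.05 | 0.5 | 0.6 | 0.912 | 84% |
| 0.05 | 0.8 | 0 | 0.684 | 93% |
| 0.05 | 0.8 | 0.6 | 0.758 | 90% |
| 0.02 | 0.5 | 0 | 0.943 | 82% |
| 0.02 | 0.5 | 0.6 | 0.956 | 82% |
| 0.02 | 0.8 | 0 | 0.853 | 86% |
| 0.02 | 0.8 | 0.6 | 0.884 | 85% |

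Interval width scales with √V. At ICC 0.05 the intervals narrow by about 4% (√0.912 = 0.955) to 17% (√0.684 = 0.827). At ICC 0.02 they narrow by about 2% to 8%.

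**Check by simulation.** Cluster log means were simulated for 152 clusters of 17 to 68 patients, with Poisson units around an assumed mean of 2.2 and a between-trust log-scale SD of 0.15. The implied ICC is 2.2²(e^0.0225 − 1)/[2.2²(e^0.0225 − 1) + 2.2] = 0.048, close to 0.05. Power rose from 0.81 to 0.85 at c = 0.5 and from 0.81 to 0.91 at c = 0.8, in line with the table.

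**Is the baseline value available?** The variable list in section 13.3 names red cell volume for pre-operative and post-operative transfusions. It names no volume for the intra-operative transfusion. For haematology it names only the amounts of other transfusions, not the units of the audited one. For those components availability rests on section 5.2.5. If the items were absent at follow-up too, the endpoints themselves could not be computed.

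**The case against.** The strongest reply is that one covariate set for all outcomes is a defensible prespecified choice, that section 16.3.6 leaves full details of the secondary analyses to the SAP, and that own-baseline adjustment would be an ordinary refinement there. Part of this stands: the outcomes are secondary, no type I error problem arises, and the gain may be small. The deferral does not settle it, because section 16.3.5 states the covariate set outright and a SAP faithful to it would carry the same list.

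The correlation c may also be low. Every arm receives feedback between the audits, section 10.1 describes trusts' responses as highly variable, and the patients differ. That limits the size of the gain but does not reverse its direction, provided that past volume predicts later volume better than the past unnecessary proportion does.

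A reader might infer more than the documents support:
- *Biased volume effects.* Randomisation keeps the comparison valid; chance imbalance is not bias.
- *Damage to the economic model.* Section 18.2 takes its effectiveness input from the rate of unnecessary transfusions, and uses audit volumes to estimate mean units per unnecessary transfusion. It does not name the adjusted volume effect as an input.
- *A gain fixed by the protocol's own ICC.* The 0.05 in section 16.2 belongs to the binary outcome.
- *A rise to 91% as a standard expectation.* That needs a correlation of 0.5 between observed trust means, hence c = 0.5/0.703 = 0.71 at ICC 0.05, and no predictive value in the planned covariate. With c = 0.5 the figure is about 84-85%.
- *Still larger gains from greater between-trust variation.* A log-scale SD of 0.30 at a mean of 2.2 units implies an ICC of about 0.17, above the 0.05 to 0.10 considered in Tables 2 and 3.

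**Conclusion.** The point holds as a modest, nearly free gain in efficiency. As written, the three patient-level volume models adjust for the baseline of a different outcome and leave out their own. Under the assumptions listed, an effect with 80% planned power would have about 84-93% at ICC 0.05 and about 82-86% at ICC 0.02, a gain of roughly 2 to 13 percentage points. None of the correlations for volume can be taken from the protocol, so this is a range and not an estimate. The point concerns precision on a secondary objective. It does not touch the primary analysis, the validity of the volume estimates or the economic evaluation, and it covers only the patient-level audit outcomes, not the trust-level BSMS and SHOT counts.

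**What to change.** In section 16.3.5, give the patient-level volume models their own covariate list: trust size, RTC, and the trust-level baseline value of the outcome being analysed. That value is the log mean red cell units (for haematology secondary outcome 4, platelet units) per audited patient in that topic's baseline audit. The baseline unnecessary proportion may stay as a further covariate. Before fixing the wording, confirm that the baseline datasets hold units for the intra-operative and the audited haematology transfusions, and state how a trust with a baseline mean of zero is handled on the log scale.

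The cost is one sentence in the protocol or SAP, one derived variable per trust and outcome from baseline audit data that go to the CTRU anyway, and at most one extra degree of freedom per model. No new data collection is needed.
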